### Primary outcome

The MDI is a self-rating scale with 12 questions. It has been extensively used in a Danish population [47] and is also thoroughly validated [48]. The questions cover the ten ICD-10 symptoms for depression, which are identical to the *Diagnostic and Statistical Manual of Mental Disorders, 4th edition* (DSM-IV) major depression diagnostic criteria except for one symptom, low self-esteem (question 4), which in DSM-IV is incorporated into a question about guilt (question 5).

The MDI holds a double function. It can be used as a diagnostic tool which, via an algorithm, can be transformed into the DSM-IV or ICD-10 categories of “mild,” “moderate,” or “severe” depression. The tool has been found to have satisfactory sensitivity and specificity with regard to the diagnosis of depression according to both the ICD-10 and DSM-IV [49]. The MDI can also be used as a rating scale, which can grade the severity of depression and this has been found to have an acceptable correlation with the Hamilton Depression Scale (HAM-D) [48].

For the purpose of the current study, the MDI will be used as a diagnostic tool at baseline with regard to the eligibility (inclusion/exclusion criteria) of the participants. Mild depression excludes participation and, as a diagnostic tool, mild depression is the presence of two core symptoms and two accompanying symptoms of depression. During the study, the MDI will be used as a rating scale to evaluate the severity and development of depressive symptoms. As a rating scale, a total MDI score (0–50 points) of 21 to 25 points corresponds to a mild depression, of 26 to 30 a moderate depression and above 31 points constitutes a severe depression. Incident depressive symptoms, defined as MDI score ≥21 any time after baseline MDI, is the primary outcome assessed using the MDI as a rating scale. Timing of outcome assessment can be seen in the SPIRIT figure (Fig. 3).

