### Statistics

Descriptive data on baseline characteristics and results will be presented as mean, SD, and *n* and presented in tabular form. Distribution of data will be tested by using data plots and by visually assessing data, and potentially continuous variables will be visualized in a matrix plot. Appropriate statistical tests will be used accordingly depending on distribution. Log transformation will be applied if applicable.

Our null hypothesis is that there will be no difference in the number of participants developing depressive symptoms (defined as a MDI score ≥21) throughout the study period between the melatonin and the placebo group. The hypothesis is assessed using Fisher’s exact test and/or the chi-squared test.

For the primary outcome analysis, a linear mixed model will be applied. The effect of age, gender, comorbidity and cardiac risk factors will be assessed by marginal analysis. Results will be assessed through an analysis on complete data generated using multiple imputation.

As a secondary analysis, the cumulative incidence of depressive symptoms will be plotted for the two groups and compared using the log-rank test assuming the absence of competing risks. Incidence of depressive symptoms (MDI score ≥21) will be analyzed using the Cox proportional hazards regression, including analysis of effects of age, gender, comorbidity and cardiac risk factors at baseline.

A principle analysis will be performed according to the intention-to-treat principle (ITT). The intention-to-treat population is defined as every patient randomized into the trial. A per-protocol analysis will also be performed. A per-protocol participant is defined as a patient who has taken medication in accordance with the protocol (at least 75%) for the first 14 days (until the follow-up visit). In cases of noncompliance with the medication before the follow-up visit (i.e., exclusion from the study), another patient will be enrolled to make up for the lost patient. Finally, a standard sensitivity analysis will be performed on the per-protocol patient population.

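### The baseline MDI total, which every patient provides at enrolment, is missing from the test of MDI ≥21 and from the factors named for the models; adjusting for it would be a nearly free gain in precision

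*Protocol article*

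**What the plan says.** The Primary outcome section of the protocol article defines the endpoint on the MDI total score: "Incident depressive symptoms, defined as MDI score ≥21 any time after baseline MDI, is the primary outcome". The scale runs from 0 to 50, and "a total MDI score (0–50 points) of 21 to 25 points corresponds to a mild depression".

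The same instrument is completed at enrolment, but in another role: "the MDI will be used as a diagnostic tool at baseline with regard to the eligibility". In that role, "mild depression is the presence of two core symptoms and two accompanying symptoms of depression". Entry therefore depends on a symptom-count algorithm, and the article states no upper limit on the entry total.

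The Statistics section then gives three analyses that bear on the MDI:

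- For the null hypothesis on MDI ≥21: "The hypothesis is assessed using Fisher’s exact test and/or the chi-squared test". No covariate enters.
- A model on the MDI: "For the primary outcome analysis, a linear mixed model will be applied". The next sentence is "The effect of age, gender, comorbidity and cardiac risk factors will be assessed by marginal analysis".
- As a secondary analysis, a Cox model of MDI ≥21, "including analysis of effects of age, gender, comorbidity and cardiac risk factors at baseline".

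The section on assignment of interventions describes 1:1 randomisation in blocks of 6 and mentions no stratification by MDI.

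**The concern.** The endpoint is the crossing of a fixed line, and patients start at different distances from it. A patient who enters at 20 becomes a case with a rise of 1 point, while one who enters at 2 and rises 18 points to 20 does not. The entry total is a natural candidate predictor of who crosses, since it is measured on the endpoint's own scale. The article names other baseline factors twice and leaves this one out both times.

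What is at stake is power for the primary question. The sample size was set close to its minimum: 116 per group are required, and the rise to 120 is explained by the block size. Variation between patients that a baseline value could explain is left in the error of the comparison.

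**Working it through.** **Inputs from the article.** Event rates 31% and 15.5%, two-sided α 0.05, power 0.80, 116 required and 120 enrolled per group (Sample size section). The prognostic strength of the baseline MDI total is not given and is varied below as an assumption.

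**Step 1: reproduce the planned sample size.** Pooled two-proportion formula without continuity correction:

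n = [1.960·√(2·p̄·q̄) + 0.842·√(p₁q₁ + p₂q₂)]² / (p₁ − p₂)²

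- p̄ = (0.31 + 0.155)/2 = 0.2325, so 2·p̄·q̄ = 2 × 0.2325 × 0.7675 = 0.3569.
- p₁q₁ = 0.31 × 0.69 = 0.2139 and p₂q₂ = 0.155 × 0.845 = 0.1310, with sum 0.3449.
- n = (1.960 × 0.5974 + 0.842 × 0.5873)² / 0.155² ≈ 2.773/0.02403 ≈ 115.4, rounded up to 116.

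This matches the article exactly, so the trial was sized for an unadjusted comparison. At 120 per arm, power is 81.5% by the same approximation and 77.9% by exact enumeration of Fisher's test, which the article also allows.

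**Step 2: variance of the risk difference after adjustment.** Let p_C(x) and p_T(x) be the event risks in control and melatonin patients with standardised baseline score x, from a logistic model calibrated to average 31% and 15.5%. With 1:1 allocation, the variance of the adjusted risk difference relative to the unadjusted one is

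[2·E{p_C(1−p_C)} + 2·E{p_T(1−p_T)} + Var(p_T − p_C)] / [2·(p₁q₁ + p₂q₂)]

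Example, odds ratio 3.0 per SD. The score explains 18.2% of the outcome variance in control and 13.9% under melatonin. The first two terms are 2 × (0.2139 × 0.818 + 0.1310 × 0.861) = 0.5755. Divided by 2 × 0.3449 = 0.6898, this gives 0.834. The last variance term brings the total to 0.842. Then 120/0.842 = 142.5, so 120 adjusted patients per arm are worth about 142 unadjusted ones.

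**Step 3: power.** Wald tests from logistic models with and without the score, 120 per arm, 3,000 simulated trials per row:

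| Assumed OR per SD | Control-arm AUC | Relative variance | 120 per arm is worth | Power, unadjusted | Power, adjusted | Gain (points) |
|---|---|---|---|---|---|---|
| 1.00 | 0.50 | 1.00 | 120 | 80.8% | 81.2% | 0.4 |
| 1.65 | 0.64 | 0.96 | 125 | 82.3% | 83.5% | 1.2 |
| 2.23 | 0.70 | 0.91 | 132 | 80.6% | 84.4% | 3.8 |
| 3.00 | 0.76 | 0.84 | 142 | 81.9% | 88.4% | 6.5 |
| 4.48 | 0.82 | 0.76 | 159 | 82.0% | 91.3% | 9.3 |

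The first row is the case of no prognostic value; its difference is simulation noise.

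**Step 4: a second model.** A latent-normal simulation (1,500 trials per setting) with correlation 0.3, 0.5 and 0.7 between baseline and highest follow-up score moved power from 0.821 to 0.845, 0.816 to 0.873 and 0.825 to 0.927. These are gains of 2.4, 5.7 and 10.2 points. A repeat run gave about 0.82 to 0.85, 0.79 to 0.86 and 0.81 to 0.92. The unadjusted figures should all be equal, so their spread shows noise of a point or two. With the top 15% of baseline scores removed, to mimic the exclusion of patients with depression at entry, the gain shrank to about 2 to 7 points but did not vanish.

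**The case against.** The strongest reply has four parts.

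- **The lists may not be adjustment sets.** Both sentences speak of the effects of patient factors, which can mean a study of predictors. Neither says that the treatment effect is adjusted for these factors and no others, and the full covariate specification may stand in an analysis plan that is not shown. This stands in part: nothing in the article says that baseline MDI will not be used. But the article does name its baseline factors, twice, and separately fixes a test without covariates.
- **The mixed-model sentence is weak evidence.** That model does not analyse a yes/no cut-off, and it could carry baseline MDI as the first repeated response. This stands. The point for MDI ≥21 rests on the unadjusted test and the Cox sentence, and the Cox model is labelled secondary.
- **The unadjusted test is sound.** It is valid and it matches the sample size calculation. This stands fully: adjustment improves efficiency and corrects no error.
- **The larger gains may be optimistic.** Eligibility removes patients with depression at entry and those with previously treated depression, which should narrow the baseline range. The simulations also assume complete outcomes, whereas no further data are collected after a patient leaves. This stands as a caution on size.

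A reader might go further and infer that the entry total largely determines who crosses 21. The documents give neither a distribution of baseline totals nor a correlation with later scores, so that cannot be said. A reader might also infer that a chance imbalance in entry MDI biases the comparison. Under randomisation it does not: such imbalance is already covered by the error rate of the unadjusted test. For the same reason, the lack of stratification by baseline score is not a defect.

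**Conclusion.** The point holds as a low-cost improvement, not as an error in the plan. The stated test of MDI ≥21 is valid, but it leaves unused a baseline value that every patient supplies. The factors named for the Cox model omit it too, and the text on the mixed model does not show that it is included.

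Over the assumed range of prognostic strength, the gain is roughly 1 to 10 points of power at 120 per arm. On the risk-difference scale this is a variance reduction of about 4% to 24%, worth some 5 to 39 patients per arm. A gain is expected if the baseline total predicts the outcome at all; its size rests wholly on an assumed strength, a baseline range not sharply cut by eligibility, and complete outcomes. If the baseline total has no prognostic value, nothing material is lost.

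**What to change.** Before unblinding, prespecify:

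- the baseline MDI total as a continuous covariate in the treatment comparison of MDI ≥21, by logistic regression with a standardised risk difference as the reported effect;
- the same covariate in the Cox model;
- in the linear mixed model, baseline MDI either as a covariate or as the first repeated response, with the choice stated;
- the unadjusted proportions and the Fisher or chi-squared result as a supporting analysis.

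The standardised risk difference matters because in logistic and Cox models the benefit appears as power, not as a smaller standard error of the ratio. On the risk-difference scale it is a true reduction in variance, and the effect stays on the scale used for the sample size.

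The cost is in the analysis plan only, with no new data or visits. It is a real change, because an adjusted model takes the lead over the stated test, and it must be documented as such. The article reports 150 of 240 patients included, blinded data analysts and no interim analysis, so at that stage the change could still be made without knowledge of results. The change does not settle whether the Fisher/chi-squared comparison or the linear mixed model is the primary analysis; the plan needs to state that as well.

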### Interventions

Patients will receive either 25 mg exogenous melatonin (intervention group) or matching placebo (control group) in an orally administered pill. Regarding the active substance each pill will contain 12.5 mg melatonin, and the placebo pill will be comparable to study medication except for the active substance. The medication will be packaged in blister packs consisting of 30 pills in each, and a total of seven blister packages will be packaged in a cardboard box (total of 210 pills). Patients will be instructed to take two pills (daily dose of 25 mg active substance) approximately 1 h before bedtime during the entire length of the study (12 weeks). Medicine compliance will be investigated at weeks 2 and 12 at clinical visits. All study medication will be produced by PharmaNord Aps. (Vejle, Denmark) in accordance with Good Manufacturing Procedure (GMP). The study medication will be shipped to the Region Zealand Hospital Pharmacy which will handle the randomization process.

If a participant withdraws their consent, they will leave the study. In the unlikely event that a female participant should become pregnant despite using reliable birth control, she will leave the study. Patients who have a recurrence of ACS during the study will be withdrawn from the study. In case of severe medical emergency (e.g., stroke or severe sepsis) requiring emergency surgery, stay in an intensive care unit, or more than 1 week of hospitalization will result in exclusion from the study. Diagnosis of a cancer during the study period will also result in withdrawal from the study. No further data will be collected from patients after leaving. However, previously collected data will be part of the final data analysis. No change in dose of study medication will be possible during the trial.

A medicine compliance of a minimum of 75% (pill count) at the clinical visits at weeks 2 and 12 are required. If the patients do not comply with these demands at either visit, they will be excluded from the study. Exclusion from the study entails stopping the study medication, and patient’s data will not be part of a per-protocol analysis. In case of medicine compliance at the first clinical visit, the data collected until this point will be part of a per-protocol analysis.

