If a patient is diagnosed with a moderate-to-severe depression on the MDI during the study, they will be referred to a psychiatrist in training attached to the study (who is blinded to the allocated treatment). The psychiatrist in training will perform a structured clinical interview (Hamilton Depression Scale) with the purpose of diagnosing depression and its severity according to the *International Classification of Diseases, version 10* (ICD-10) criteria. Patients with a moderate-or-severe depressive episode according to the Hamilton Depression Scale and clinical assessment will be withdrawn from the study and offered open treatment for depression via the patient’s general practitioner (GP). All outcome data collected until the eventual termination in the study will be part of the final analysis. If the patient is diagnosed with a mild depression on the MDI, they will be allowed to continue in the study. The patient will be monitored using the MDI and phone calls according to the study protocol. In case of symptom progression on the MDI into moderate to severe depression, the participant will be referred to the psychiatrist in training as described above.

Patients will be contacted by phone seven times (every 2 weeks) during the trial to assure compliance and to promote their retention during follow-up. The patients will be reminded to fill in the relevant study questionnaires, reminded to take study medication, and monitored for occurrence of any adverse reactions, or changes in other medication since last contact with study investigators.

The participants are allowed to participate in all offered concomitant care at their regional cardiology department (e.g., cardiac rehabilitation). Startup of any medical antidepressant treatment in the trial period is prohibited and will lead to exclusion from the trial.

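### A patient who starts an antidepressant for depression before any recorded MDI score of 21 or more leaves the trial without an event, and the planned analyses ignore why

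*Protocol article*

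**What the plan says.** The event is defined under Primary outcome: "Incident depressive symptoms, defined as MDI score ≥21 any time after baseline MDI, is the primary outcome". Statistics repeats the threshold for the null hypothesis, which is tested by Fisher's exact and/or the chi-squared test, and for the Cox model. The abstract gives two-weekly MDI assessment.

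Interventions sets these rules on leaving:
- Antidepressants: "Startup of any medical antidepressant treatment in the trial period is prohibited and will lead to exclusion from the trial".
- Recurrent events: "Patients who have a recurrence of ACS during the study will be withdrawn from the study". Cancer and severe medical emergencies are handled in a similar way.
- After leaving: "No further data will be collected from patients after leaving". Data collection says the same of patients who do not comply with the intervention protocol.
- Before leaving: "All outcome data collected until the eventual termination in the study will be part of the final analysis".
- The trial's own depression route: "If a patient is diagnosed with a moderate-to-severe depression on the MDI during the study, they will be referred to a psychiatrist in training".

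The secondary analysis in Statistics plots cumulative incidence by arm, "compared using the log-rank test assuming the absence of competing risks", and adds Cox regression. Multiple imputation is mentioned next to the linear mixed model for the primary outcome.

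**The concern.** A patient may become depressed between two questionnaires, be given an antidepressant by a doctor outside the trial, and be excluded before any score of 21 is recorded. The outcome itself causes that exit.

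The log-rank and Cox analyses treat the patient as censored. They assume that the later hazard equals that of patients still followed, which is implausible for someone who has just been treated for depression. In the binary comparison the article does not state the patient's status. If it is imputed under missing at random from scores below 21, the imputation does not use the reason for leaving.

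At stake are lost events in a design with little slack (116 per arm required, 120 planned) and, if loss differs between arms, a biased estimate.

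**Working it through.** **1. Who is lost and who is not**

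| Path | MDI ≥21 recorded before leaving? | Status |
|---|---|---|
| Mild on the rating scale (21 to 25), stays in | Yes | Event |
| Referred on a moderate-to-severe MDI, then withdrawn | Normally yes: moderate is "of 26 to 30 a moderate depression", above 21 | Event, because earlier data are kept |
| Antidepressant started outside the trial after a score ≥21 | Yes | Event |
| Antidepressant started for depression with no score ≥21 so far | No, and none can follow | No event; censored in log-rank and Cox; binary status not stated |

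Only the last row is a defect.

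**2. The plan's own sample size**

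Inputs from Sample size: p1 = 0.31, p2 = 0.155, two-sided α = 0.05, power 0.80. With pooled variance and no continuity correction:

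n = [1.96·√(2·p̄·q̄) + 0.8416·√(p1q1 + p2q2)]² / (p1 − p2)²

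Here p̄ = 0.2325, so 2p̄q̄ = 0.3569, and p1q1 + p2q2 = 0.3449.

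n = (1.1709 + 0.4943)² / 0.02403 = 115.4, rounded up to 116. The stated figure reproduces.

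Power at 120 per arm = Φ[(0.155·√120 − 1.1709) / 0.5873] = Φ(0.897) = 0.815.

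**3. Equal loss in both arms**

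The share f of true cases that leave on an antidepressant before any score ≥21 is not in the article, so f is an assumption. Every lost case is scored as a non-event. Observed rates are (1 − f)·0.31 and (1 − f)·0.155.

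For the log-rank column, HR = ln(0.845)/ln(0.69) = 0.454, held fixed. Expected events are d = 120 × the sum of the two rates, and power = Φ(½·√d·|ln HR| − 1.96).

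| f | Placebo | Melatonin | Power, two proportions | Events d | Power, log-rank |
|---|---|---|---|---|---|
| 0 | 31.0% | 15.5% | 0.815 | 55.8 | 0.839 |
| 5% | 29.5% | 14.7% | 0.789 | 53.0 | 0.820 |
| 10% | 27.9% | 14.0% | 0.760 | 50.2 | 0.799 |
| 20% | 24.8% | 12.4% | 0.697 | 44.6 | 0.751 |

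The risk ratio stays at 0.50 in every row, so equal loss costs power only. In patients, 20% is 0.20 × 37.2 = 7.4 placebo cases and 0.20 × 18.6 = 3.7 melatonin cases.

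**4. Unequal loss (also assumed)**

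| Lost, placebo | Lost, melatonin | Observed rates | Risk ratio | Power |
|---|---|---|---|---|
| 20% | 10% | 24.8% v 14.0% | 0.56 | 0.567 |
| 10% | 20% | 27.9% v 12.4% | 0.44 | 0.854 |

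The first dilutes the true ratio of 0.50 and the second exaggerates it.

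**5. Competing risks**

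Withdrawal for recurrent ACS, cancer or a severe emergency stops observation but does not prevent depression, so it raises a censoring question. Death does prevent later depression and is the clear competing event. Log-rank and Cox can still be read as cause-specific when deaths are censored. The plotted one-minus-Kaplan-Meier curve, however, is not the actual 12-week risk if deaths occur.

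**The case against.** The strongest reply is that few patients can be affected. MDI is completed every two weeks with phone reminders, earlier data are kept, and the psychiatric route starts from a score already above the threshold. Previous pharmacologically treated depression is an exclusion criterion. The competing-risk wording concerns a secondary analysis over only 12 weeks, and the planned comparison of reasons for and timing of leaving would help to show unequal loss. All of this stands and limits the size. It does not give the remaining patients a correct status.

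A reader might infer more than the article supports:
- *Depression cases in general are censored as depression-free.* They are not, because a score of 21 or more before exit remains an event. Nor does censoring declare a patient depression-free; it assumes the same later hazard.
- *Excluded patients are non-events in the binary test.* The article does not say so. It plans multiple imputation, although whether that covers the Fisher or chi-squared test is unclear. The power figures above are conditional on that scoring.
- *The medical withdrawal rules contradict the assumption of no competing risks.* Those withdrawals are censoring; only death is plainly competing.
- *A real benefit would be hidden.* Equal loss leaves the risk ratio at 0.50, and unequal loss can exaggerate the effect as well as dilute it.

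**Conclusion.** The point holds in a narrow form. Antidepressant start for depression without a prior MDI score of 21 or more is outcome-related, ends observation and is not an event. The planned log-rank and Cox analyses treat that exit as uninformative, and imputation under missing at random would not correct the binary comparison.

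The number of such patients cannot be derived from the article. Under the assumed 5% to 20% equal loss, scored as non-events, power at 120 per arm is 0.79 to 0.70 instead of 0.815. Under the assumed unequal losses the risk ratio is 0.44 or 0.56 instead of 0.50, so no direction of bias can be claimed. The stated 116 per arm is correct and not in question.

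**What to change.** In Statistics, before unblinding:

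1. Pre-specify an analysis of both the binary and the time-to-event outcome in which antidepressant start for depression, by recorded indication and without a prior score of 21 or more, counts as an event on its start date. Report it beside the MDI-only result. With 150 of 240 patients already included (Status of the trial), a parallel analysis is easier to defend than a new primary endpoint.
2. Delete the clause that assumes competing risks away. Treat death as the competing event in the cumulative incidence plot, and describe the log-rank and Cox results as cause-specific.
3. Treat medical withdrawals as censoring, with a sensitivity analysis for informative censoring.

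The cost is a little extra analysis. Medication changes are already monitored at each phone call, and reasons for leaving are already to be compared between arms. The one addition is the indication for each antidepressant start, so that starts for other reasons can be set apart. No withdrawal or treatment rule changes.

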### Sample size

Sample size is calculated on the basis of a conservative assumption that 31% of patients following ACS will develop depressive symptoms [4] which we assume can be reduced to 15.5% by melatonin treatment. Power calculation is based on two-sided test and, with a power of 0.80 and a significance level of 5% (*α* = 0.05), the required sample size in each group is 116. There are no interim efficacy analyses planned. The patients will be randomized in blocks of 6 and, therefore, the study will proceed until 120 patients have been enrolled in each arm.

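### The per-protocol set has conflicting definitions, and uncapped replacement of early non-compliers leaves the number randomised open; the ITT set itself is clearly defined

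*Protocol article*

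**What the plan says.** All references are to the protocol article.

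**Compliance and the per-protocol set**
- Interventions sets the requirement: "A medicine compliance of a minimum of 75% (pill count) at the clinical visits at weeks 2 and 12 are required". A patient who fails at either visit is excluded from the study, stops study medication and is left out of the per-protocol analysis.
- The next sentence of Interventions adds: "In case of medicine compliance at the first clinical visit, the data collected until this point will be part of a per-protocol analysis".
- Statistics defines a per-protocol participant as one who has "taken medication in accordance with the protocol (at least 75%) for the first 14 days". It says nothing about week 12. The same population is then used for a sensitivity analysis.

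**Number of patients**
- The abstract gives a total of 240, and Sample size says that "the study will proceed until 120 patients have been enrolled in each arm".
- Statistics says that when a patient is excluded for non-compliance before the follow-up visit, "another patient will be enrolled to make up for the lost patient". It gives no cap, no expected rate and no larger total.

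**ITT and data after exclusion**
- Statistics makes ITT the principal analysis and includes in it all who were randomised.
- Data collection says that nothing further is collected once a participant stops medication or otherwise fails to comply. Interventions likewise ends data collection when a patient leaves, but keeps what was collected before.

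**The concern.** Two analysts working from this text could build different per-protocol sets. The difference affects both the per-protocol analysis and the sensitivity analysis run on the same population. One reading would also remove MDI scores recorded after week 2, including any that had already reached the event threshold of 21, because of a pill count made when treatment ends.

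The replacement sentence raises a separate question: does 240 count everyone randomised, or only those left after early non-compliers have been replaced? The answer decides when recruitment stops. Replacement may also look like a remedy for lost information in the principal analysis, which it is not. The excluded patient stays in the ITT set with an outcome that is unobserved after about two of the twelve weeks. Early non-compliance could plausibly be related to side effects or low mood, and a new patient does not supply the missing outcome.

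**Working it through.** **1. Per-protocol status of one patient.** Take a patient with at least 75% compliance at week 2 and below 75% at week 12.

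| Source | Status | Data used |
|---|---|---|
| Statistics, per-protocol definition | per-protocol participant | not restricted |
| Interventions, exclusion sentence | out | none |
| Interventions, sentence that follows | in | up to the first visit only |

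The Statistics rule tests only a small part of treatment:
- scheduled pills over 12 weeks: 84 days × 2 = 168
- scheduled pills over 14 days: 14 × 2 = 28
- share tested: 28/168 = 16.7%

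Under the third row, on the two-weekly MDI schedule given in the abstract, scores from weeks 4 to 12 would be dropped although they had been recorded.

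**2. The plan's own sample size.** Inputs from Sample size: "31% of patients following ACS will develop depressive symptoms", "which we assume can be reduced to 15.5% by melatonin treatment", power 0.80 and two-sided α = 0.05. With p1 = 0.31, p2 = 0.155 and mean p = 0.2325, the pooled-variance formula without continuity correction is

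n = [1.960·√(2p(1−p)) + 0.842·√(p1(1−p1) + p2(1−p2))]² / (p1−p2)²

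- √(2 × 0.2325 × 0.7675) = 0.5974, times 1.960 = 1.171
- √(0.2139 + 0.1310) = 0.5873, times 0.842 = 0.494
- n = (1.171 + 0.494)² / 0.155² ≈ 115.4, rounded up to **116** per group

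The stated 116 is reproduced. At 120 per arm the same formula gives power 0.815.

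**3. Number randomised under replacement.** The document gives no week-2 non-compliance rate, so the rate d is an assumption. If replacement continues until 240 patients are compliant at week 2, N = 240/(1−d), rounded up.

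| d | N randomised | Excluded early, still in ITT |
|---|---|---|
| 5% | 240/0.95 = 253 | 13 |
| 10% | 240/0.90 = 267 | 27 |
| 15% | 240/0.85 = 283 | 43 |
| 20% | 240/0.80 = 300 | 60 |

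If 240 instead counts everyone randomised, N = 240 and the replacement sentence has no effect. Under replacement, the share of the ITT set with truncated follow-up is still about d (13/253 and 27/267 are about 5% and 10%). Replacement adds complete patients but does not lower the proportion with missing outcomes.

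**4. Power without replacement.** Take 240 randomised, with no outcome from non-compliers.

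| d | Per arm with outcome | Power |
|---|---|---|
| 0 | 120 | 0.815 |
| 5% | 114 | 0.795 |
| 10% | 108 | 0.773 |

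These figures use the approximation that reproduces 116. Fisher's exact test, which Statistics also names, gives about 0.779 at 120 per arm.

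**The case against.** The strongest case on the other side is that the per-protocol passages can be read together. Statistics says who is a per-protocol participant, and Interventions says which of that participant's data count. The two sentences in Interventions then form a rule and an exception: excluded patients are out, except that data to the first visit are kept if they were compliant there. This reading is possible, but the text does not state it. It also produces the least attractive result, since MDI data already collected after week 2 are discarded because of a week-12 pill count. Using compliance over the whole treatment period to define a per-protocol set is ordinary practice and is not the complaint.

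A reader might also infer three stronger things that the document does not support:
- **That the ITT set is undetermined.** Statistics defines its membership explicitly, and Interventions keeps data collected before a patient leaves. Only its final size and the outcomes after exclusion are open, and multiple imputation is planned.
- **That the ITT arms are no longer comparable.** A replacement is one more randomised patient, and the excluded patient stays in the set. Selection on compliance affects the per-protocol set. In ITT the problem is missing outcomes.
- **That 120 per arm cannot be met.** Allocation is 1:1 in blocks of 6, and the regional pharmacy holds the list. The text is ambiguous about whether 120 is counted before or after replacement, which does not make it unachievable.

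**Conclusion.** The point holds for two items. First, the per-protocol set is worded in ways that give up to three different results for the same patient, and the sensitivity analysis on that population inherits the problem. Second, the number randomised is not fixed. It is 240 on a literal reading of the stop rule, or about 253 to 267 if replacement runs until 240 are compliant at week 2 and 5% to 10% are not. Those rates are assumptions; at 20% the total would be 300.

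Replacement does not restore information to the principal analysis, because replaced patients remain in ITT and their data collection ends. The calculated 116 per group is correct, and the principal analysis set is properly defined.

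**What to change.** 1. **Per-protocol set.** Reconcile Interventions and Statistics into one definition, applied in the same way to the per-protocol and sensitivity analyses. It should not delete MDI data collected before non-compliance is established. The sponsor chooses the compliance rule.
2. **Number randomised.** State that 240 counts all patients randomised and delete the replacement sentence. Alternatively, keep an allowance for early non-compliance by stating the inflated randomised total and the assumed rate behind it.
3. **Follow-up.** Amend Data collection, and the matching sentence in Interventions, so that the MDI continues to be collected from consenting patients who are excluded for non-compliance. The questionnaire already goes out by email link, with paper as a fallback.

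**Cost.** The main cost is a wording amendment plus a modest amount of continued questionnaire follow-up. The per-protocol set will be smaller if the sponsor chooses a rule that reaches beyond the first 14 days. Without replacement, and if non-compliers give no outcome, power is about 0.795 (5%) or 0.773 (10%) instead of 0.815; any outcomes recovered under item 3 reduce that loss. The inflated-total option instead costs about 13 to 27 extra patients at the same rates. The article reports 150 of 240 already included, so any replacements already made cannot be undone. Their number should be reported and those patients kept in ITT.
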